### ***Cross over design***

A cross over design is proposed for the following reasons: HIV has a complex disease course, and it is acknowledged that there may be many different mechanisms for the DSN so it is desirable if the participant acts as their own control. It is considered that the disease course will not significantly deteriorate in the follow up period of 15 weeks, although the baseline pain intensity will be measured at the start of each treatment intervention. It is anticipated that the follow up period is not too long to see a significant attrition rate. There will be two sub-groups: those stable on ARV with DSN and those not on ARV drugs. Secondly, the disease process is fairly stable over the proposed 14 weeks and the survival times for most participants will be more than proposed trial period.

Washout period: The SAMF 8 cites a plasma  $t_{1/2}$  of 10-50 hours, but also notes that the nortriptyline metabolite is active. The rule of thumb would be 5 half-lives, but in this case, you'd need to track down the metabolite's elimination. (Handbook of Basic Pharmacokinetics including Clinical Applications (6th edition). Ritschel WA and Kearns GL. APHA, Washington, 2004) gives a  $t_{1/2}$  for nortriptyline of 14-90 hours. On that basis, you'd be looking at a wash-out of at least 450 hours, or 18.75 days. Personal correspondence [name]

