### **Randomisation**

The randomisation allocation provided by the manufacturers of the placebo and active product. Participants will receive either regime A or regime B in a random manner. One regime will contain 6 weeks of active substance, followed by three weeks washout, then with 6 weeks of placebo, the other will contain 6 weeks of placebo followed by three weeks washout, then 6 weeks of active substance. Patients will be randomly allocated via a concealed allocation; the randomisation will be generated by block randomisation methods.

[figure not shown]

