| Day 13                  | The study nurse will call to enquire as to adverse effects, pain score and any other problems, and advice on the next dosage. If pain has abated significantly the dose will be left at four tablets at night. If not the dose will be increased to six tablets at night. I                       |
| Week 3 day 15           | The study nurse will call to enquire as to adverse effects, pain score and any other problems, and advise to stay at the same dosage for the next 4 weeks                                                                                                                                         |
| Visit 3.0 Week 3 day 21 | Visit to study site. Check diary, questionnaire administered, medication check, discussion and information as required with participant, reimbursement, referral as required                                                                                                                      |
| Week 4 day 28           | The study nurse will call to enquire as to adverse effects, pain score and any other problems, and advise to stay at the same dosage for the next 3 weeks                                                                                                                                         |

|                         |                                                                                                                                                                                                                                                                                                                                                                                                                                                                                                             |
|-------------------------|-------------------------------------------------------------------------------------------------------------------------------------------------------------------------------------------------------------------------------------------------------------------------------------------------------------------------------------------------------------------------------------------------------------------------------------------------------------------------------------------------------------|

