| Week 5 day 35           | The study nurse will call to enquire as to adverse effects, pain score and any other problems, and advise to stay at the same dosage for the next 2 weeks                                                                                                                                                                                                                                                                                                                                                   |
| Visit 6.0 Week 6 day 42 | 
 
1. Visit to study site Check diary, questionnaire administered, medication check, discussion and information as required with participant, reimbursement, referral as required Collection of demographic data(Appendix I)
 
2. Collection of clinical data(Appendix II)
 
3. Assessment of peripheral neuropathy and other symptoms(Appendix III); if present refer to Palliative care
 
4. Assessment of coexisting pain medication
 
 |
| Week 7 day 49           | The study nurse will call to enquire as to adverse effects, pain score and any other problems                                                                                                                                                                                                                                                                                                                                                                                                               |
| Week 8 day 56           | The study nurse will call to enquire as to adverse effects, pain score and any other problems                                                                                                                                                                                                                                                                                                                                                                                                               |

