| Visit 9.0 Week 9 day 63 | Visit to study site Check diary, questionnaire administered, medication check, discussion and information as required with participant, reimbursement, referral as required. Patient to receive new drug pack                                                                                                                                                                                                                                                                                               |
| Week 10 Day 66          | The study nurse will call to enquire as to adverse effects, pain score and any other problems, and advice on the next dosage. If the pain has abated significantly the dose will be left at one tablet at night. If not, the dose will be increased to two tablets at night for three nights.                                                                                                                                                                                                               |
| Day 69                  | The study nurse will call to enquire as to adverse effects, pain score and any other problems, and advice on the next dosage. If the pain has abated significantly the dose will be left at two tablet at night. If not, the dose will be increased to three tablets at night for three nights.                                                                                                                                                                                                             |

|                                                                   |                                                                                                                                                                                                                                                                                                                                                                                                                                                            |

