| Visit 12.0 Week 12 day 82                                         | 
5. Visit to study site Check diary, questionnaire administered, medication check, discussion and information as required with participant, reimbursement, referral as required Collection of demographic data(Appendix I)
 
6. Collection of clinical data(Appendix II)
 
7. Assessment of peripheral neuropathy and other symptoms(Appendix III); if present refer to Palliative care
 
8. Assessment of coexisting pain medication
 |
| Day 91                                                            | The study nurse will call to enquire as to adverse effects, pain score and any other problems, and advice to stay on the same dosage for the next 2 weeks                                                                                                                                                                                                                                                                                                  |
| Day 98                                                            | The study nurse will call to enquire as to adverse effects, pain score and any other problems, and advice to stay on the same dosage for the next 1 weeks                                                                                                                                                                                                                                                                                                  |
| Exit procedure Week 15 is the exit visit and visit to study site. | Check diary, questionnaire administered, medication check, pain intensity score, clinical examination and discussion and information as required with participant, reimbursement, referral as required. Information on study results feedback session                                                                                                                                                                                                      |

[figure not shown]

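### Two period 1 telephone calls hold the dose one week too long, to day 49, and no visible row stops the drug at day 42; staff who follow the calls would leave a 14-day washout, below the protocol's own 18.75-day minimum

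*Protocol*

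**What the plan says.** **Design text.** The Randomisation section of the protocol sets out the active-first regime as "6 weeks of active substance, followed by three weeks washout", then six weeks of placebo; the other regime reverses the order. The Trial abstract and the washout paragraph under Ethics review also give three weeks. Under Cross over design, the protocol applies a rule of five half-lives to the active metabolite. It cites a half-life "for nortriptyline of 14-90 hours" and concludes that this calls for "a wash-out of at least 450 hours, or 18.75 days".

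**Period 1 schedule (Follow up procedures).** The day 15 call holds the dose for 4 weeks. The day 28 call is to "advise to stay at the same dosage for the next 3 weeks", and the day 35 call is to "advise to stay at the same dosage for the next 2 weeks". The day 42 visit begins with "Check diary, questionnaire administered, medication check, discussion and information as required with participant" and continues with data collection and assessments. It mentions neither stopping nor returning tablets. The calls on days 49 and 56 ask about adverse effects and pain and give no dosing advice. At day 63 the entry reads "Patient to receive new drug pack".

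**Period 2 schedule.** The day 91 call is to "advice to stay on the same dosage for the next 2 weeks", and the day 98 call gives 1 week. The exit visit is at week 15 (day 105).

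**The concern.** The two period 1 calls instruct dosing into the first week of the washout, and nothing visible in the schedule countermands them. The washout protects the crossover comparison. The Study Summary defines the primary objective by pain at the start and end of each six-week period, so the day 63 score is the baseline for period 2.

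In participants given amitriptyline first, drug still present on day 63 would lower the baseline of their placebo period. The fall in pain on placebo would look smaller than it is, and the advantage of amitriptyline larger. Placebo-first participants have no such carry-over. Some participants might also stop on day 42 and others on day 49, so washout length would depend on which instruction was followed.

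**Working it through.** **1. The protocol's minimum.** Inputs: five half-lives and a longest metabolite half-life of 90 h (Cross over design). 5 × 90 = 450 h; 450 / 24 = 18.75 days. The stated figure is reproduced.

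**2. Where each call ends.** End day = call day + 7 × weeks of hold.

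| Call | Hold | Ends | Intended end |
|---|---|---|---|
| Day 15 (period 1) | 4 weeks | 15 + 28 = 43 | 42 |
| Day 28 (period 1) | 3 weeks | 28 + 21 = 49 | 42 |
| Day 35 (period 1) | 2 weeks | 35 + 14 = 49 | 42 |
| Day 91 (period 2) | 2 weeks | 91 + 14 = 105 | 105 |
| Day 98 (period 2) | 1 week | 98 + 7 = 105 | 105 |

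Days 91 and 98 are days 28 and 35 of period 2 (91 − 63 = 28; 98 − 63 = 35). The same two calls therefore carry one week more in period 1 than in period 2. The day 15 call overshoots by one day only and leaves 63 − 43 = 20 days, above the minimum.

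**3. Washout.**
- Intended: 63 − 42 = 21 days = 504 h.
- Following the day 28 and day 35 calls: 63 − 49 = 14 days = 336 h, which is 450 − 336 = 114 h short.
- Longest half-life for which five half-lives fit: 504 / 5 = 100.8 h intended; 336 / 5 = 67.2 h if the calls are followed. The cited range reaches 90 h.

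**4. Drug remaining on day 63.** Fraction = 2^(−hours / half-life).
- At 90 h: 336 h is 3.7 half-lives, leaving 7.5%; 504 h is 5.6 half-lives, leaving 2.1%.
- At 50 h (the upper end cited for amitriptyline itself): 336 h leaves 0.9%.
- At 16 h (the average cited for amitriptyline): essentially nil.

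**5. Effect on the comparison.** Two assumptions are needed: relief is proportional to exposure, and the full effect is 2 points (the difference used in Sample size calculations). At 90 h the period 2 baseline of an amitriptyline-first participant is lowered by 2 × 0.0752 = 0.150 points. Placebo-first participants are unaffected, so the average over the two sequences is 0.150 / 2 = 0.075, about 0.08 points. The intended 21 days would give 2 × 0.0206 / 2 = 0.021 under the same assumptions. At 50 h, the 14-day figure is 2 × 0.0095 / 2, about 0.01.

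**6. Visit windows, a separate matter.** Visit windows allows 3 days either side. With every call counted correctly, a day 42 visit held on day 45 and a day 63 visit held on day 60 leave 60 − 45 = 15 days.

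**The case against.** The strongest reply is that the protocol fixes a three-week washout in three places and that the schedule itself mostly points to day 42. The text before the table has the final dose taken for 4 weeks, and the day 15 call ends on day 43. The day 42 visit is face to face, comes after both faulty calls and includes a medication check. The calls on days 49 and 56 drop the advice to stay on the dose, which fits participants being off drug. Each regime is described as containing six weeks of active substance, which suggests a supply planned for six weeks. A figure after the schedule is not shown, and the participants' written instructions and the standard operating procedures are not in the document, so a stop step may exist elsewhere.

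Most of this stands. It shows what was intended, and it rules out the reading that the protocol plans a 14-day washout. It does not remove the contradiction. The two calls are dosing instructions, they conflict with the design text, and no visible row resolves the conflict. Pack size is not stated, so the document does not show whether tablets would run out. A participant held at a low dose could have some left if packs were sized for the maximum dose.

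A reader might also combine the faulty calls with an early day 63 visit and quote 11 days (60 − 49). That adds a visit-window issue that exists whatever the calls say, so it should not be used to enlarge this point.

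**Conclusion.** The point holds as an internal contradiction in the dosing schedule. The day 28 and day 35 calls are each one week too long, and no visible row stops the drug at day 42. The resulting washout of 14 days, against the 18.75 days that the protocol requires of itself, is conditional on staff following the calls over the design text.

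A reader might infer that the crossover comparison is seriously compromised. The numbers do not support that. The bias is at most about 0.08 points against the planned difference of 2. That ceiling needs every participant to have a 90 h half-life and to keep dosing to day 49, and it needs relief proportional to exposure. At 50 h the bias is about 0.01 points. An analysis of end-of-period scores alone would be affected little. The correction is worth making because the instruction is wrong, it concerns the safeguard on which the design depends, and it costs almost nothing to put right.

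**What to change.** - **Calls.** Change the day 28 call to 2 weeks and the day 35 call to 1 week. Alternatively, word the calls on days 15, 28 and 35 as holding the dose until the day 42 visit, which also removes the one-day overshoot at day 15.
- **Day 42 visit.** Add: stop study drug, collect remaining tablets, record the date of last dose.
- **Separate safeguard against the visit windows.** At the day 63 visit, give the period 2 pack no sooner than 19 days after the last dose, and make the 3-day window subject to this rule. A last dose on day 45 gives 45 + 19 = day 64, so the visit can still fall on days 64 to 66, inside its window of days 60 to 66.

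The cost is a few lines of wording in the follow-up schedule and under Visit windows, and one recorded date. No visits are added.

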## Trial abstract

A double blind randomised controlled trial to assess the effectiveness of amitriptyline compared to placebo in the management of moderate to severe HIV- related peripheral neuropathy. A cross over design will be used and 124 adult male and female volunteer participants with moderate to severe HIV related neuropathic pain will be followed up for a total of 15 weeks. Sixty two participants will be clinically and virologically stable on ARV drugs and 62 will not be in ARV therapy or intending to start in the next four months. In the first six weeks participants will be given either amitriptyline or identical looking placebo titrated to either effect or a maximum dose of 150mg. Then following a three week 'washout' period, participants will be 'crossed-over' to the other arm and titrated to either effect or a maximum dose for 6 weeks. Pain intensity will be measured on a daily basis and recorded into a pain diary by the participant and regular telephonic contact will be maintained between the study nurse and the participants. Pain intensity using tools validated for neuropathic pain, as well as other data will be collected at face to face interviews at each of the 5 scheduled follow up visit. Data collected will include information on adverse events, physical functioning and quality of life.

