## **Product information**

Amitriptyline has antidepressant properties belonging to the tricyclic group. Indicated use is for management of depressive illness, nocturnal enuresis, and pain relief in chronic pain syndromes. It is well absorbed orally, has a half life of between 10 and 50 hours (average 16 hours). It is extensively metabolized in the liver, involving microsomal hepatic enzymes and eliminated over several days, primarily in the urine.

Contraindications are early post-myocardial infarct period and heart block. Use with caution is recommended in patients with: hyperthyroidism, or on thyroxine therapy; arrhythmias; epilepsy; prostatic enlargement; closed angle glaucoma or impaired liver function.

Amitriptyline has no drug interactions with ARV therapy. Drug interactions include those with antihistamines, antipsychotics, anti-cholinergic type anti parkinsonian agents, cimetidine, fluoxetine, paroxetine, steroids, including oral contraceptives and MAOI drugs. It is not to be used in pregnancy.

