### ***Screening procedure***

Patients agreeing to participate will undergo screening. The following will happen during this visit:

1. Information session on the study. Posters and group recruitments will be supported by one-to one information sessions
2. Assess eligibility for study
3. Written consent will be obtained to have a short eligibility questionnaire administered and a test for ankle reflexes and vibration sense. See appendices
4. Inform participant of eligibility status then either thank participant for involvement in screening and referral to palliative care or other services if appropriate. Or if eligible invite them to information session in the study now or at a time convenient to them.

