### ***Baseline procedure***

The following is the procedure for the baseline visit:

1. Detailed information session on the study
2. Time to consider participation and invite questions and clarification
3. If agrees to join study then administer written informed consent. If not or changes mind then thank the participant for their time
4. For those enrolled collection of demographic data(Appendix 3)
5. Collection of clinical data(Appendix 4)
6. Assessment of peripheral neuropathy(Appendix 5);
7. Review eligibility criteria and if still eligible and consenting then randomization will occur
8. Participant will be given arm treatment, pain diary and written and verbal instructions. They will receive an airtime voucher or telephone card for R28 per month for the duration of the study and a telephone number to call should they need to call the study team

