### **Side effects**

Side effects will be continually monitored throughout the study as part of symptom control. (Appendix IV)

| Amitriptyline |
|----------------------|
| Dry mouth            |
| Sedation             |
| Weight gain          |
| Confusion            |
| Dizziness            |
| Palpitations         |
| Constipation         |

|       |
|-------|
| Other |
|-------|

Patients who develop side effects will be assessed by a doctor. Patients assessed as having serious adverse events will be withdrawn from the study, and reasons recorded. The total period of the study will be 6 weeks from enrolment. After being enrolled, subjects will be monitored for pain relief, symptom control and quality of life by the nurse, after which an intervention will be put in place. Monitoring will be done weekly by a professional nurse. Intervention can be one of the following:

- Increase the dose, and continue with the trial
- Maintain the dose, and continue with the trial
- Stop the drug because of adverse events, and drop from the study

For those that have been found to be not effective, alternative treatment will be offered.

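### The day-63 drug pack, the first amitriptyline for the placebo-first sequence, is issued with no stated condition on pregnancy or newly started interacting drugs

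*Protocol*

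**What the plan says.** The Protocol lists two eligibility checks. The Screening procedure has "Assess eligibility for study", and the Baseline procedure has "Review eligibility criteria and if still eligible and consenting then randomization will occur". No later call or visit repeats either.

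Under Randomisation, one regime gives active drug first, and "the other will contain 6 weeks of placebo followed by three weeks washout, then 6 weeks of active substance". The period-2 pack is handed over at Visit 9.0, week 9, day 63. The follow-up schedule lists a diary check, questionnaire, medication check, discussion, reimbursement and referral for that visit, and ends with "Patient to receive new drug pack".

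Product information says of amitriptyline "It is not to be used in pregnancy" and "Contraindications are early post-myocardial infarct period and heart block". The Exclusion Criteria bar pregnancy or planned pregnancy; MAOI, other tricyclic and anti-epileptic drugs; recent infarction, arrhythmia and heart block; and a history of urinary retention, urinary hesitancy or closed angle glaucoma.

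Several safeguards exist. The Trial abstract says of the five follow-up visits: "Data collected will include information on adverse events, physical functioning and quality of life". Nurse calls on days 49 and 56 ask about adverse effects and other problems. The Side effects section withdraws participants with serious adverse events and, for adverse events generally, offers "Stop the drug because of adverse events, and drop from the study".

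**The concern.** A crossover has two treatment starts, and this Protocol makes only the first conditional on eligibility. In the active-first sequence the baseline review comes directly before first exposure. In the placebo-first sequence nine weeks separate them, and six weeks on placebo say nothing about whether amitriptyline is now safe for that person.

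A woman who has become pregnant, or a participant who has been prescribed an MAOI or another tricyclic since baseline, need not have had any adverse event to report. If staff follow the schedule as written, that participant receives the pack. At stake is a first exposure that the Protocol's own entry rules would have refused. The primary comparison, sample size and power are not in question.

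**Working it through.** The Protocol states no figure to reproduce here. The check is a timeline, a head count, and a comparison of each exclusion with the safeguards that could detect it.

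**Timing of first exposure (placebo-first).** Six weeks of treatment plus three weeks of washout: 42 + 21 = 63 days, which matches Visit 9.0. Taking baseline as day 0 and the 3-day window from Visit windows, first exposure falls 63 − 3 = 60 to 63 + 3 = 66 days after the last listed eligibility review.

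**Most recent contacts.**
- Clinical data collection is listed at Visit 6.0 (day 42): 63 − 42 = 21 days before. With windows on both visits the range is (63 − 3) − (42 + 3) = 15 to (63 + 3) − (42 − 3) = 27 days.
- Calls on days 49 and 56 come 63 − 49 = 14 and 63 − 56 = 7 days before. The 21 days are therefore not a period without contact.

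**What follows dispensing.** Dose increases are made by telephone and can reach six tablets by day 75, which is 75 − 63 = 12 days later. At 25 mg per tablet (Guidelines for introducing amitriptyline), 6 × 25 = 150 mg. The next listed site visit is day 82, or 82 − 63 = 19 days after dispensing. Visit 9.0 is thus the last scheduled face-to-face contact before the maximum dose may be reached.

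**Number starting amitriptyline at day 63.** Enrolment is 124. The allocation ratio is not stated; 1:1 is assumed, so 124 / 2 = 62. Sample size calculations allow about 10% loss to follow-up. If all of it occurs by day 63, 62 × 0.90 = 55.8, about 56 remain; if none does, 62. For scale only, 1% of 56 to 62 is 0.56 to 0.62 participants.

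**Which exclusions the existing steps detect.**
- *New infarction, arrhythmia, heart block, urinary retention, liver or renal failure.* Each is an untoward medical occurrence, so it fits the adverse-event definition whether or not the drug caused it. Calls and visits ask for such events, and the stopping rule applies. Largely covered.
- *Pregnancy.* Planned pregnancy is barred at entry, but no later step asks about pregnancy, and it need not be reported as an adverse event. Not reliably covered.
- *New MAOI, other tricyclic or anti-epileptic drug.* The drug assessment listed at day 42 is confined to pain medication. The day-63 medication check has neither a defined scope nor a linked action. Not reliably covered.
- *TB treatment.* In these documents anti-TB drugs appear as a cause of neuropathy (Background), which is a confounding reason. They are not among the interactions or cautions in Product information. This is no ground for withholding drug on safety.

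The Side effects section offers three actions: increase, maintain, or stop for adverse events. None of them withholds period 2 because an exclusion is newly met.

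**The case against.** The strongest reply is that the Protocol is silent here, not wrong. Visit 9.0 includes a questionnaire, a medication check and a discussion before the pack is given. The visit forms and SOPs are named under Appendices but not shown, as is a figure after the visit schedule, and any of them could hold the questions. That stands, and it limits the claim to what the text makes conditional. It does not remove the point: whether trial drug may be dispensed is normally settled in a protocol and not left to an analysis plan, and here the first dispensing is conditional while the second is not.

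It is also fair that weekly contact, the broad adverse-event definition and the stopping rule cover most of the list. A reader might infer from the missing eligibility review that participants with a new infarction or heart block would routinely be started on amitriptyline. The documents do not support that: such events should surface in the calls or at the visit, and serious ones lead to withdrawal. Nor should 56 to 62 be read as a count of people at risk. It is everyone due a first active pack at that visit, and no rate of newly met exclusions is given.

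Finally, a check at day 63 does nothing for an exclusion first met in the middle of a treatment period, and a question misses an unrecognised pregnancy. Both limits stand. They make the fix partial, but it would still be useful.

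**Conclusion.** The point holds in a narrow form. The text issues the period-2 pack unconditionally, this is the first amitriptyline for the placebo-first sequence, and the listed safeguards do not reliably pick up pregnancy or a newly started interacting drug. It concerns about 56 to 62 dispensings, assuming 1:1 allocation and between all and none of the anticipated 10% loss by day 63, at 60 to 66 days after the last listed eligibility review. The number of participants who would actually meet an exclusion is unknown and probably small.

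This is an improvement to consider, held with medium confidence because the forms and SOPs are not visible. It has no bearing on the sample size or the validity of the primary result.

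**What to change.** At Visit 9.0, before dispensing, ask and record for every participant:
- whether she is pregnant or planning a pregnancy;
- whether an MAOI, a tricyclic other than study drug, or an anti-epileptic has been started;
- confirmation that no myocardial infarction, arrhythmia, heart block, urinary retention or closed angle glaucoma has arisen since baseline.

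Withhold the pack if any item is met. Applying the check to both sequences keeps the blind. Leave out TB treatment and the other exclusions that serve only to limit confounding. Leave out prior amitriptyline use as well, since blinded staff cannot answer it for study drug. A pregnancy test is not needed for this change.

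Amend the Side effects section at the same time. Its present option couples stopping the drug with leaving the study. A participant whose pack is withheld should stop study drug but continue pain follow-up to week 15, so that the planned intention-to-treat analysis keeps the data.

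The cost is a few recorded questions at an existing visit. A few participants may lose period-2 treatment, including some who would have received placebo, which slightly reduces the paired treatment data. If the unseen forms already ask these questions, one sentence making dispensing conditional on the answers, plus the amended stopping rule, is enough.
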